#### *Practitioner evaluation*

*Therapist alliance* will be assessed using the Working Alliance Inventory short form (WAI-SR) [78], which is based on Bordins’ original model of alliance. The full Working Alliance Inventory (WAI) consists of 36 items on a seven-point Likert scale [79]. WAI-SR comprises 24 items – 12 items that measure a therapist’s experience of the client and 12 items measuring the client’s experience of the therapist, each of these focusing on tasks, goals and bonds. The items are scored on a seven point Likert scale with 1 being never and 7 being always. WAI-SR is highly correlated with the full WAI and can serve as an adequate substitute (that is, the bond scales have a correlation of .94 and .91, the goal scales .91 and .86, and the task scales .83 and .87) [78].

*Programme dose, programme integrity and programme compliance* will be assessed using a range of measures designed for this study to capture the duration, frequency and focus of the sessions. Programme integrity will be assessed using the PuP Therapist Experience Measure (TEM) [9], which examines the extent to which the client perceives the key concepts of the programme to have been covered. It is based on the Therapist Adherence Measure developed for use in multi-systematic therapy [80], which found high scores to be predictive of the client outcome.

### Data-collection process

Data will be collected by a researcher who is blind to study arm, in the respondent’s home or at a drug treatment centre. Study participants will be requested not to disclose their group allocation to the researcher, and loss of blinding will be recorded and taken into account at the analysis stage. The data will comprise a range of self-report questionnaires that are robust to loss of blinding, and independent observations of the parent and infant, which will be rated externally to the research team. The researcher will provide assistance with the completion of self-report questionnaires where this is required. Data will be collected at baseline, immediately post-intervention and at the 6-month follow-up.

### Process evaluation

#### *Aim*

The aim of the process evaluation is twofold.

First, it is to identify the extent to which factors such as the amount of intervention received and practitioner evaluation affect the impact of the intervention. This will involve exploratory statistical analyses to examine the inter-relationships between the individual contexts of both families and centres, and the treatment mechanisms for change embedded within the programme in terms of their impact (that is, the outcomes obtained).

Second, it is to enhance understanding of the user and provider experiences of the new service. A range of data will be collected from participants who refuse to take part in the study or drop out of the intervention or study; this will include quantitative demographic data and qualitative data to explore the reasons for non-participation or discontinuation. In-depth interviews will also be conducted with: a) practitioners and supervisors following the training and during the delivery of the intervention, b) a range of stakeholders (for example, partner agencies, local commissioners and national opinion leaders) and c) a purposive sample of participating parents. The latter will be selected using quantitative outcome data to identify study participants who show change and those who show no change, and the aim of the interviews will be to gain a better understanding of the factors that contributed to these outcomes.

### Data-collection methods

Candidates for interview will be invited to take part in an interview by letter, and will be provided with an information sheet explaining why they have been invited to take part and the wider study context and a consent form. Interviews will be conducted at a time and location convenient to the stakeholder. Where necessary, telephone interviews will be conducted. With the permission of the interviewee, all interviews will be recorded.

The interviews will be conducted using a semi-structured interview schedule, which will provide a list of key topics to be explored. Interviews with stakeholders will focus on the following: the experience and adequacy of the training and ongoing supervision, issues relating to referral and embedding of the PuP service within the wider service context and the perceived benefits and difficulties relating to the delivery of the service. Interviews with the purposive sample of service recipients will focus on the following: perceptions about the PuP service and provider, aspects of the services that were experienced as favourable or unfavourable, ways in which the service helped or hindered recovery, experience of other services and so on.

### Data management and analysis

Interview data will be fully transcribed and coded using the qualitative data analysis package NVivo 8. Thematic analysis will be undertaken to identify the key themes that emerge across the data. A narrative summary of the key themes identified will be presented using quotations selected on the basis of their capacity to demonstrate some aspect of the identified theme.

### Economic evaluation

A prospective economic evaluation, conducted from a NHS and personal social services perspective, will be integrated into the trial. The economic assessment method will, as far as possible, adhere to the recommendations of the NICE Reference Case [81]. Primary research methods will be followed to estimate the costs of delivering the PuP programme, including development and training of accredited providers, the cost of delivering the intervention, participant monitoring activities, and any follow-up or management. Broader resource utilisation will be captured through two principal sources: (i) participant questionnaires, adapted from the Client Services Receipt Inventory, administered at each follow-up point; and (ii) data from routine data-collection systems. Unit costs for health and social care resources will largely be derived from local and national sources and estimated in line with best practice. Primary research using established accounting methods may also be required to estimate unit costs. Costs will be standardised to current prices where possible. Cost-effectiveness analysis will be undertaken on two main outcome measures: parent–infant interaction (CARE-Index) and child abuse potential (CAPI) at 6 months.

Results will be presented using incremental cost-effectiveness ratios and cost-effectiveness acceptability curves generated via non-parametric bootstrapping. This accommodates sampling (or stochastic) uncertainty and varying levels of willingness to pay for reductions in the primary outcomes of interest. Additionally, net benefit statistics will be estimated. A series of sensitivity analyses will explore the effects of uncertainty surrounding key parameters on the incremental cost-effectiveness ratios. One such analysis will adopt a societal perspective incorporating costs to other sectors of the economy, direct costs to trial participants and their partners, informal care provided by family and friends, and productivity losses.

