### Sample size

Dawe and Harnett [9] found an effect size (ES) of 0.92 using the Child Abuse Potential Inventory (CAPI) scores, in an RCT of the PuP programme in Australia with parents of children aged 3 to 8 years. This is a large change and the current study, which is being conducted with a younger population of children (under 2.5 years), should therefore be powered to detect a much smaller change.

Power calculations for the current study show that in the region of 54 women are required in each arm of the study to detect a change in the region of 0.5 ES with 80% power and 0.05 significance. Considerably more families (that is, in excess of 147 per arm) would be required to be confident of detecting a change that is smaller than this (that is, 0.45 ES). Allowing for dropout in the region of 5% [9] necessitates that approximately 114 families are recruited to the study (that is, 57 in each arm).

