### Data analysis

All data will be analysed using an intent-to-treat analysis, unless significant deviations from the intended treatment arm are detected, in which case a per protocol analysis may also be conducted. Descriptive statistical summaries (for example, medians and ranges, means and variances, or contingency tables, depending on the variable distribution and type) will be presented for the primary and secondary outcome measures at each time point. Baseline data will be scrutinised to check comparability between treatment arms and to highlight any characteristic differences between the six trial recruitment sites. Any disparities found will be added to subsequent models to compensate for these differences.

Data collected from families who were approached but refused to take part and those who dropped out will also be analysed and examined for trends (using only basic information such as consenting participant age, gender and intervention arm), alongside qualitative data concerning the reasons for dropping out. We will also investigate potential contamination between intervention groups, as described in the Randomisation section above.

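### The service-receipt questionnaire is placed at follow-up points only and no baseline cost is planned, so the incremental cost will be less precise than it need be (minor; cheap to improve)

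*Protocol article*

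**What the plan says.** The Economic evaluation section states: "Broader resource utilisation will be captured through two principal sources". The first is "participant questionnaires, adapted from the Client Services Receipt Inventory, administered at each follow-up point". The second is "data from routine data-collection systems", with no time window given. The section describes incremental cost-effectiveness ratios, bootstrapped acceptability curves and net-benefit statistics. It mentions neither a baseline cost nor any covariate for costs. It fixes the effect measures as follows: "Cost-effectiveness analysis will be undertaken on two main outcome measures: parent–infant interaction (CARE-Index) and child abuse potential (CAPI) at 6 months".

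The Data-collection process section gives the general timetable: "Data will be collected at baseline, immediately post-intervention and at the 6-month follow-up". The Data analysis section says of imbalances seen in the baseline data: "Any disparities found will be added to subsequent models to compensate for these differences". It does not mention costs.

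**The concern.** The article states when the questionnaire is given, and that timing leaves baseline out. The Data-collection process section lists baseline separately from the post-intervention and 6-month assessments, and Subsidiary analyses draws the same contrast. The plain reading of a follow-up point is therefore one of the two later visits.

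The two halves of the cost-effectiveness comparison are then treated differently. On the effect side, the Primary analysis section uses baseline CAPI, comparing change from baseline by ANCOVA. On the cost side, no baseline quantity is named. If families' service use before entry predicts their use afterwards, an arm that happens to contain heavier users will look more expensive for reasons unrelated to the programme, and nothing planned would correct for it.

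Cost effectiveness is part of the stated study objective and the trial is small, so precision on the cost side matters. Prior service use that is not recorded at entry is hard to recover later, because families would have to recall it across the treatment period.

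**Working it through.** The article gives no figure for this point, so there is none to reproduce. The check has two parts.

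**Wording.**
- Questionnaire: follow-up points only (Economic evaluation).
- Routine data: a source is named, but its period is not (Economic evaluation).
- General schedule: includes a baseline visit but does not say that service receipt is recorded there (Data-collection process).
- Baseline disparities: to be added to later models (Data analysis). A model can adjust only for what has been measured, and costs are not mentioned.

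So no baseline cost from the questionnaire is planned, a baseline cost from routine data is left open, and no cost adjustment is named.

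**Scale.** Inputs:
- n = 54 per arm, the number the Sample size section requires. It plans 57 per arm, 114 in total, before dropout of about 5%.
- r, the within-arm correlation of baseline with follow-up cost. The article does not give it, so 0.3, 0.5 and 0.7 are assumed.

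All results are in units of the between-family SD of cost.

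1. SD of a chance difference in mean baseline cost = √(2/n) = √(2/54) = 0.192. The 95% range is ±1.96 × 0.192 = ±0.38. With 57 per arm these are 0.187 and ±0.37.
2. Unadjusted SE of the follow-up cost difference, by the same formula: 0.192.
3. Adjusted SE = 0.192 × √(1 − r²). The share of variance removed is r².
4. Shift in the unadjusted cost difference when the baseline imbalance lies at its 95% limit = r × 0.377.

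| Assumed r | Variance removed (r²) | Adjusted SE | Shift at 95% limit |
|---|---|---|---|
| 0.3 | 9% | 0.184 | 0.11 |
| 0.5 | 25% | 0.167 | 0.19 |
| 0.7 | 49% | 0.137 | 0.26 |

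The gain can also be expressed as a sample size. An unadjusted comparison would need 54/(1 − r²) families per arm to match the adjusted one: 54/0.91 = 59, 54/0.75 = 72 and 54/0.51 = 106.

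These are linear-model approximations. Skewed costs would make them rougher.

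**The case against.** A reader might infer that costs have no baseline value at all and that the comparison cannot be corrected. The article does not support that. The sentence that schedules the questionnaire also names routine data, which are not tied to visits and could reach back before randomisation. Their window is unstated, which is not the same as absent. Routine systems may miss participant, informal-care and productivity costs, but those enter only a societal-perspective sensitivity analysis; the main perspective is NHS and personal social services.

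A reader might also infer that the incremental cost is biased. It is not: randomisation makes the unadjusted difference unbiased in expectation. The planned bootstrap represents sampling uncertainty, chance imbalance included. It does not narrow that uncertainty or correct an imbalance that has occurred. Nor does variation in standard services between sites add much to the concern, since the Randomisation section stratifies by centre using minimisation. What remains is variation between families within a site.

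It would also be too strong to say that every other measure has a baseline. Working alliance and programme integrity cannot exist before treatment starts.

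The strongest objection is that a journal article condenses a fuller protocol, where the questionnaire timetable, recall period and cost covariates may be set out. That disposes of any complaint about missing detail. It does not dispose of the timing that the article does state: if the full protocol includes a baseline administration, the article's wording is wrong on that point. Finally, the gain depends on an undocumented correlation. At r = 0.3 the SE falls only from 0.192 to 0.184, about 5%.

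**Conclusion.** The point holds as a cheap improvement of minor severity. As written, the plan takes self-reported service use only after randomisation, sets no pre-randomisation period for routine data and names no adjustment of costs for baseline costs. The consequence is lost precision and avoidable exposure to chance imbalance in the incremental cost and in the net-benefit results built on it.

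The size rests on 54 evaluable families per arm and on the assumed correlations. Adjustment would remove from 9% to 49% of the variance of the cost difference, and only the part of any imbalance that baseline cost predicts. That service use persists over time is itself an assumption. If the correlation is low, little is lost under the present plan.

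**What to change.** 1. Give the adapted Client Services Receipt Inventory at the existing baseline visit in both arms, before randomisation, with a stated recall period. If the full protocol already does this, correct the article's wording to say so.
2. Request the same pre-randomisation period from the routine data systems where they can supply it, and state the window.
3. Include baseline cost as a covariate in the incremental-cost and net-benefit models, fixed in advance and not made conditional on an observed disparity.

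The cost is one more short questionnaire at a visit that takes place anyway, a wider date range in the routine-data request and one model term. The downside is a slightly longer baseline visit. The Trial status section says recruitment is only about to start, so at the time of writing the change could cover all participants.

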### Data analysis

All data will be analysed using an intent-to-treat analysis, unless significant deviations from the intended treatment arm are detected, in which case a per protocol analysis may also be conducted. Descriptive statistical summaries (for example, medians and ranges, means and variances, or contingency tables, depending on the variable distribution and type) will be presented for the primary and secondary outcome measures at each time point. Baseline data will be scrutinised to check comparability between treatment arms and to highlight any characteristic differences between the six trial recruitment sites. Any disparities found will be added to subsequent models to compensate for these differences.

Data collected from families who were approached but refused to take part and those who dropped out will also be analysed and examined for trends (using only basic information such as consenting participant age, gender and intervention arm), alongside qualitative data concerning the reasons for dropping out. We will also investigate potential contamination between intervention groups, as described in the Randomisation section above.

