### Randomisation

Randomisation will be stratified by centre using minimisation [52], and consenting parents will be randomly allocated to one of two arms, using a computer-generated numbers table (using Stata v7) by an independent statistician. The intervention arm will receive the Parents under Pressure programme alongside standard services for substance-dependent parents, and the control arm will receive standard services alone, which will vary by site but will mostly be adult facing and linked to the management of addiction and relapse, alongside the implementation of child protection services as appropriate. Standard services will also provide families with access to universal health and parenting support, children’s centre support and self-help groups in addition to the more targeted support from drug and alcohol treatment services.

To reduce bias and contamination, study staff and researchers involved with delivering the PuP intervention will have no contact with families in the control group. All data will be collected by a researcher who is blind to group allocation (see Data-collection process). Some contamination within centres may still occur, however, because there is a small population of families at each site and families in the intervention group may pass ‘helpful’ information to families in the control group. Furthermore, participants may reveal their treatment allocation to the researcher whilst undergoing data-collection activities, such as the qualitative interviews. An assessment of the extent to which contamination has occurred will be made as part of the process of data collection (for example, recording any unmasking of group allocation during interviews with families and asking if families know others in the study). If levels of contamination are found to be high in either study group, an extra confounder variable denoting contaminated controls will be added to the analysis and the effects of this contamination investigated (see Data analysis section). However, we do not expect that contamination between groups will be a significant issue because the ‘dose’ received by control families will be low compared with that received by the intervention group (that is, the intensive 20-week programme).

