#### *Primary analysis*

Changes in the CAPI score between baseline and at the 6-month follow-up will be compared for the intervention groups using ANCOVA with the site where the family was recruited used as an independent confounder.

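### Primary-model covariates are to be chosen by baseline imbalance, so the model is not fixed in advance and baseline BCAPI is not explicitly secured

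*Protocol article*

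**What the plan says.** The Data analysis section of the protocol article sets out a screening step: "Baseline data will be scrutinised to check comparability between treatment arms and to highlight any characteristic differences between the six trial recruitment sites". The next sentence turns the result of that screen into a modelling rule: "Any disparities found will be added to subsequent models to compensate for these differences". No candidate variables, test or threshold are given, and the rule is not confined to sensitivity analyses.

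Primary analysis follows directly. "Changes in the CAPI score between baseline and at the 6-month follow-up will be compared for the intervention groups", and the method is given as "using ANCOVA with the site where the family was recruited used as an independent confounder". Site is the only covariate named. (The section writes CAPI; the instrument listed as primary outcome is the brief form, BCAPI.)

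Under Randomisation, "Randomisation will be stratified by centre using minimisation", with two arms.

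**The concern.** In a properly randomised trial, a baseline difference between arms is a chance event. A variable's observed imbalance says nothing about whether it predicts the outcome, and prediction is what makes a covariate worth adjusting for. A rule driven by imbalance can bring in variables of no prognostic value and leave out useful ones that happen to be balanced.

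The pool to be screened is large. Data-collection instruments lists eight outcome measures (BCAPI, CARE-Index, BITSEA, DASS-21, PSI-SF, DERS, PAI-BOR and Timeline Follow-back), several with subscales, and demographic data come on top. With no definition of a disparity, two analysts following the text could fit different primary models to the same data.

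Two things are at stake. The first is whether the primary result is tied to one model chosen beforehand. The second is whether the covariate most likely to matter, the baseline score of the primary outcome, is certain to be in that model.

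**Working it through.** **Inputs from the protocol.** Sample size states that "54 women are required in each arm of the study to detect a change in the region of 0.5 ES", with 80% power and significance 0.05. Sidedness is not stated; two-sided is used below.

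**Assumptions, because the protocol gives no values.** Correlation r between baseline and follow-up score; number of screened variables k; a p<0.05 screen; screened variables independent of each other and, apart from the baseline score, unrelated to outcome. SD = 1. Site is left out of the simulated models.

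**1. The plan's own figure.** Two-sided, unadjusted: n = 2(1.960 + 0.842)² / 0.5² = 62.8, so 63 per arm. One-sided: 2(1.645 + 0.842)² / 0.5² = 49.5, so 50. Neither gives 54. The dropout step does reproduce: 54 / 0.95 = 56.8, so 57. The mismatch is a separate matter. It is noted only because 54 per arm is the base used here, at which unadjusted two-sided power is 0.74.

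**2. How often chance would change the model.** P(at least one disparity) = 1 − 0.95^k.
- k = 5: 23%
- k = 10: 40%
- k = 12: 46%
- k = 20: 64%

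Correlated subscales would lower these figures.

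**3. What baseline BCAPI is worth.** Power = Φ(0.5 / (SD × √(2/54)) − 1.96), where √(2/54) = 0.192. The SD is √(2(1 − r)) for a change score without baseline as covariate and √(1 − r²) with it.

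| r | Change score, no baseline covariate | Baseline as covariate |
|---|---|---|
| 0.3 | 0.59 | 0.78 |
| 0.5 | 0.74 | 0.85 |
| 0.7 | 0.92 | 0.95 |

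For r = 0.5 the change-score SD is 1, giving Φ(2.598 − 1.96) = 0.74. The adjusted SD is 0.866, giving Φ(3.000 − 1.96) = 0.85.

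**4. Separating the rule from the missing baseline score.** Simulated power at 54 per arm, effect size 0.5, r = 0.5, with every variable imbalanced at p<0.05 added:

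| Model | k = 10, 5,000 runs | k = 12, 4,000 runs | k = 12, repeat |
|---|---|---|---|
| Change score | 0.727 | 0.723 | 0.714 |
| Change score + rule | 0.731 | 0.716 | 0.710 |
| Fixed baseline covariate | 0.847 | 0.830 | 0.832 |
| Fixed baseline covariate + rule | 0.841 | 0.822 | 0.822 |

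Adding the rule moves power by between +0.4 and −1.0 percentage points. Adding the baseline score moves it by 10.7 to 12.0 points (0.830 − 0.723 = 0.107; 0.847 − 0.727 = 0.120). In the 4,000-run simulation the rule cost 0.7 and 1.3 points at r = 0.4 (0.654 to 0.647 without baseline, 0.805 to 0.792 with it), and 0.6 and 0.5 points at r = 0.7 (0.917 to 0.911, 0.951 to 0.946).

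**5. Type I error.** With the rule applied mechanically, rejection under no effect ranged from 0.034 to 0.053 across simulations. The Monte Carlo standard error is about √(0.05 × 0.95 / 4000) = 0.003, so there is no sign of inflation.

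**The case against.** **ANCOVA normally implies a continuous covariate.** With only arm and site, both categorical, the primary model would be an analysis of variance, so the authors may well have meant baseline BCAPI to be included. A change score adjusted for baseline gives the same treatment estimate as a follow-up score adjusted for baseline, and on that reading the power gap disappears. This stands as a fair reading, but the text names only site and does not settle the matter.

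**The rule may not reach the primary analysis.** That section gives its own model, and Subsidiary analyses provides mixed models to explore confounding. However, the rule speaks of subsequent models without exception, and the primary analysis comes next. The plain reading includes it, though not beyond doubt.

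**The sentence also covers site differences.** These are real and not products of randomisation. That is correct, but site is already in the primary model, and it does not justify selecting on differences between arms.

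**A threshold could sit in an analysis plan.** It could, but a threshold would only make selection on imbalance more orderly. The rule itself is stated here and would have to be reversed.

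**A stronger reading is tempting: that the rule raises the false-positive rate.** If disparities at p<0.20 could be kept or dropped at will and the most favourable fit reported, type I error would be about 7% to 9%. The protocol describes no such conduct. It says that disparities will be added, not that they may be, and mentions neither that threshold nor choosing among fits.

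**Conclusion.** The point holds as a stated method that should be replaced. Covariates would be selected by chance imbalance under an undefined criterion, so the primary model is not fixed before the data are seen. Under the assumed p<0.05 screen of 12 independent variables, about 46% of trials would have their model altered by chance; correlation among the scales would reduce this.

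The statistical cost of the rule itself is small: about 1 percentage point of power and no inflation of type I error when applied mechanically. These results assume that the added variables are unrelated to outcome.

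A reader might infer that the rule lowers power from about 85% to 74%. It does not. That gap comes from baseline BCAPI being absent, which is a possible reading of Primary analysis but not an established one. If it is absent, power is about 0.71 to 0.74 against 0.83 to 0.85 at r = 0.5, and the gap widens at lower r and narrows at higher r. Nor does the plan forgo every useful covariate, since site, the stratification factor, is named in advance.

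**What to change.** Replace the sentence in Data analysis with a covariate list fixed before unblinded data are seen. For the primary model, name baseline BCAPI, centre and, if wanted, one or two prognostic variables already collected, such as child age or baseline DERS. For each secondary outcome, use the matching baseline score and centre. State in Primary analysis that the baseline score is a covariate. Report baseline comparisons between arms and sites descriptively. Keep any adjustment prompted by observed imbalance as a labelled sensitivity analysis.

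The cost is a few sentences of text. No further data are needed, and Trial status says recruitment is only starting, so the change can be made before outcome data exist.
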